### Study participants

A stroke team member at the hospital will identify potential patients, and a physiotherapist will assess patient eligibility based on the following inclusion: (1) > 18 years of age; (2) any gender; (3) admitted with a diagnosis of stroke with onset within 2 weeks; (4) Brunnstrom stages of stroke recovery between 2 and 4 for the upper extremity; (5) able to follow directions; (6) no severe cognitive impairments that could interfere with patient participation; (7) consent to treatment by the patient; and (8) Alpha-Functional Independence Measure (Alpha-FIM) score of > 40. Patients will be excluded based on several criteria: (1) medically unstable patients; (2) lack of motivation; (3) recurrent/chronic stroke; (4) recent upper extremity musculoskeletal injuries with movement restrictions; (5) receptive or global aphasia; (6) delirium; (7) unilateral neglect; and (8) visual field defect.

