### Group assignment

#### Sample size estimates

The sample size and effect size were calculated based on a previously published study [24], using the G* power software. A sample of 18 will be required in each group to detect a difference in the primary outcome measure (FMA-UE) with an effect size (Cohen’s d) of 1.15 and a statistical power of 0.80 at a one-sided type one error of 0.05.

Based on the above calculation, a total of 36 patients will be recruited and assigned to the MT (n = 18) or control group (n =18) using a random sampling method. Randomization will be done prior to the baseline assessment with a statistical software program that generates this sequence. Random numbers will be assigned according to the order of patients’ admission to the hospital. To *conceal allocation*, random group allotment will be managed by a social worker who will not be involved in the assessment or intervention to minimize the confounding and contamination. Refer to Fig. 1 for the study process.

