### Statistical analysis

#### Data analysis

Data will be analyzed using the SPSS software version 23. Demographic characteristics and baseline scores will be compared using the independent *t*-test and the chi-squared test for continuous variables (such as age and time since stroke) and dichotomous variables (gender, dominance, affected side, and type of lesion), respectively. A two-way repeated analysis of variance (ANOVA) with time and group effects will be used to analyze between-group differences. We will administer both intention-to-treat and per-protocol analyses to determine the effectiveness of the proposed intervention [27]. The level of significance will be set at *P* < 0.05. Patients will be considered as being compliant if they perform at least 80% of the original MT protocol. The compliance will be reported using the four ways recommended by Hawley-Hague et al. (i.e., completion, attendance, duration adherence, and intensity adherence) [28]. In addition, CONSORT will be used to report this RCT to facilitate reading and quality assessment.

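### Allocation of 36 patients spanning Brunnstrom stages 2 to 4 is described without stratification and the analysis names no severity term, so a moderate chance imbalance is left uncontrolled.

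*Protocol article*

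**What the plan says.** All locations are in the protocol article.

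- **Study participants.** A physiotherapist checks eligibility, and one criterion is "Brunnstrom stages of stroke recovery between 2 and 4 for the upper extremity". Stage is therefore known before anyone is allocated.
- **Sample size estimates.** The text says that "36 patients will be recruited and assigned to the MT (n = 18) or control group (n =18) using a random sampling method". On the mechanism it adds: "Randomization will be done prior to the baseline assessment with a statistical software program that generates this sequence". It continues: "Random numbers will be assigned according to the order of" admission, with a social worker holding the allotment. No stratum, block or minimisation factor is mentioned.
- **Outcome measures and data collection.** Brunnstrom stage is listed among the characteristics recorded at the initial assessment. FMA-UE, WMFT and the Modified Barthel Index are measured at baseline and at 4 weeks.
- **Data analysis.** The arms are compared at baseline: "Demographic characteristics and baseline scores will be compared using the independent" t-test or the chi-squared test. For the treatment comparison, "A two-way repeated analysis of variance (ANOVA) with time and group effects will be used to analyze between-group differences". Neither stage nor any other severity variable is given a place in the model.

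**The concern.** Brunnstrom stage grades how far motor recovery of the arm has already gone, so it plausibly predicts both 4-week scores and the amount of further change. With 18 patients per arm and three stages admitted, chance alone can leave one arm noticeably milder than the other. An exact 18/18 split does not prevent this, because it fixes the totals and not the mix of stages.

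The plan holds the information needed to guard against this at two points, allocation and analysis, and as described uses it at neither. Baseline significance tests would only describe an imbalance; they do not correct for it. At stake are the precision and credibility of a single small trial on its two primary outcomes.

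**Working it through.** **The plan's own figure.** The documents give no probability of imbalance, no stage mix and no definition of a marked imbalance, so there is nothing to reproduce on this point. The sample size calculation ("d) of 1.15 and a statistical power of 0.80 at a one-sided type one error of 0.05") enters only as the planned effect, d = 1.15.

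**Inputs.** From the article: 36 patients, 18 per arm, stages 2 to 4, d = 1.15, and the SMD of 0.47 quoted in its Critical review section. Assumed: the number K of the 36 patients who fall in a given severity category, and a correlation r of 0.5 to 0.9 between baseline and 4-week scores.

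**Step 1: chance of an uneven split in one category.** With the arms fixed at 18/18, the number X of the K patients who land in the MT arm is hypergeometric:

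P(X = x) = C(K, x) · C(36 − K, 18 − x) / C(36, 18).

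For K = 12, a difference of 4 or more means 8 vs 4 or worse. The one-sided terms are 0.1070 (x = 8), 0.0317 (x = 9), 0.0053 (x = 10) and 0.0005 (x = 11 or 12 together). They sum to 0.1445, and doubling gives 0.289.

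| K in the category | Arms differ by 4 or more | Arms differ by 6 or more |
|---|---|---|
| 9 | 0.121 | 0.018 |
| 12 | 0.289 | 0.075 |
| 14 | 0.305 | 0.086 |
| 18 | 0.318 | 0.094 |

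A difference of 4 patients is 4/18 = 22 percentage points.

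**Step 2: the same question on a continuous severity scale.** The standard error of the difference in baseline means is SD × √(2/18) = 0.333 SD. The chance of a difference above 1/3 SD is P(|Z| > 1) = 0.317. Above 0.5 SD it is P(|Z| > 1.5) = 0.134.

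**Step 3: what reaches the treatment comparison.** With two time points, the group-by-time term compares mean change between the arms. With equal SDs at both times, a baseline difference of 1/3 SD shifts that comparison by (1 − r) × 1/3 SD:

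- r = 0.5: 0.167 SD, which is 0.167/1.15 = 15% of the planned effect and 0.167/0.47 = 35% of the quoted SMD.
- r = 0.9: 0.033 SD, which is 3% of the planned effect and 7% of the quoted SMD.

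**Step 4: error rate given that an imbalance has occurred.** Simulating the change comparison under no treatment effect, among draws with a baseline difference of at least 1/3 SD, gives a two-sided false-positive rate of 9.2% at r = 0.5 and 5.9% at r = 0.9. One-sided, with the imbalance in the favourable direction, it is 16% and 9%. Over all randomisations the rate is nominal.

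**Step 5: precision.** In SD² units, the residual variance is 2(1 − r) for change and 1 − r² for the 4-week score adjusted for baseline. The ratio of the second to the first is (1 + r)/2: 0.75 at r = 0.5 and 0.95 at r = 0.9.

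**Step 6: effect of stratifying.** With permuted blocks within each of the three stages, the arms can differ in a stage by at most 1 patient (blocks of 2) or 2 patients (blocks of 4). The chance of a 4-patient difference falls from 0.289 (K = 12) to 0. With only two strata, stage 2 against stages 3 and 4 together, and 12 patients per stage, stages 3 and 4 are still divided by chance. For 24 patients split 12/12, the chance of 8 vs 4 or worse in stage 3 is 0.220.

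**The case against.** **Nothing is stated wrongly.** Unstratified randomisation is a legitimate design. The article never says outright that allocation is unstratified, and a full protocol that is not shown could name strata. This stands, and it is why the point is an improvement and not an error. What remains is that the article describes the sequence, its timing, its order of use and its custodian, and that description reads as a single list.

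**The probability depends on the cut-off.** This also stands. The plan defines no marked imbalance. The 29 to 32% needs a 4-patient cut-off and a third to a half of patients in the category. With 9 patients it is 12%, and for a 0.5 SD difference it is 13%.

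**The analysis already uses baseline.** Largely right. A reader might infer that an imbalance in stage could by itself produce or conceal the planned effect. The documents do not support that: comparing change subtracts the starting level, and the remaining shift is 3 to 15% of d = 1.15 under the assumed correlations. It reaches 35% only against the smaller SMD of 0.47 and at the least favourable correlation. A spurious shift in FMA-UE points cannot be derived either, because the article does not say how much change differs between stages.

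**Chance imbalance is part of the type I error.** Correct. The argument for stratifying rests on precision and on the interpretation of this one trial.

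**Covariate adjustment alone would do most of the work.** Fair. Baseline FMA-UE and WMFT are collected and are finer measures than stage. A reader might think adjustment untrustworthy with 18 per arm, but nothing in the documents supports that. A prespecified baseline covariate is a sound complement and could serve as the minimum remedy.

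**Conclusion.** The point holds in moderate form. As described, severity is controlled neither in the allocation nor by a model term, although stage is available for both. The chance of a 4-patient difference in a severity category is about 29 to 32% if 12 to 18 patients fall in it, and 12% if 9 do. For a 6-patient difference it is 7.5 to 9.4% with 12 to 18 patients. Such an imbalance could moderately distort the estimate of this one trial, because comparing change leaves severity-dependent recovery in place. It does not bias the test across randomisations.

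These figures rest on an assumed stage mix, an assumed correlation of 0.5 to 0.9, arms of exactly 18, and the reading that one unstratified sequence is used. This is an optional improvement, worth making before enrolment because stratification cannot be added to patients already allocated. The Trial status section reports that none had been recruited.

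**What to change.** **Sample size estimates (allocation text).** Stratify the randomisation list by the Brunnstrom stage recorded at screening, using small permuted blocks whose size varies at random. The social worker holds the lists, and block sizes are disclosed to no one who screens, treats or assesses. Use all three stages, or use two strata (stage 2 against stages 3 and 4) and accept some residual imbalance between stages 3 and 4.

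**Data analysis.** Include the stage stratum in the primary model. If the repeated-measures ANOVA is kept, stage must enter with its interaction with time, because a stage main effect alone does not alter the group-by-time comparison. Preferably, analyse each 4-week score adjusted for its own baseline value and stage.

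**Cost.** One or two degrees of freedom for the stage term (two or three strata), two or three lists in place of one, and arm totals possibly a patient or two off 18/18. No extra patients, visits or staff are needed. Blocking within strata makes upcoming assignments slightly easier to guess in an open-label, single-centre trial; concealing and varying the block size limits this. If the allocation cannot be changed, prespecified adjustment for baseline score and stage still recovers most of the benefit.

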### Blinding

Pre- and post-test assessments will be performed by a physiotherapist who will be blinded to group allocation (assessor blinding). Patient education will be provided by a research assistant who will neither be involved in outcome assessment nor with implementing regular rehabilitation interventions. The research assistant will ensure that the patient understands the parameters of the exercise intervention, mirror placement, and unilateral arm execution (nonparalytic arm should be moved and not the paralyzed arm) and masters the MT technique.

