### Participant timeline

Participant timeline was developed according to the SPIRIT guideline and is presented in Table 3.

**Table 3 Tab3:** Timeline of screening, recruitment, randomization, interventions, and assessments

Time point	Study period		
	0 week (w)	4 w	Closeout (4 w)
Enrollment			
Eligibility screen	x		
Informed consent	x		
Allocation	x		
Intervention			
Experimental group	x	x	
Control group	x	x	
Assessments			
Demographics	x		
FMA-UE	x	x	
WMFT	x	x	
MBI	x	x	

*FAM-UE* Fugl-Meyer Assessment-upper extremity, *WMFT* Wolf Motor Function Test, *MBI* Modified Barthel Index

Rehabilitation interventions are crucial during the first 4 weeks post-stroke as it is a critical time for neural plasticity and recovery [17]. Therefore, the present study will be initiated within 48 to 72 h of patient admission in the acute care unit and will be continued for 4 weeks following the initial assessment. Following admission to an acute stroke unit, screening and informed consent and baseline outcome assessments will be completed within 48 to 72 h. The mirror therapy education will commence immediately after the baseline assessment and end in 4 weeks.

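### Randomisation precedes the baseline assessment in an open-label trial, so allocation can be known when the first of the two analysed measurements is scored

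*Protocol article*

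**What the plan says.** The protocol article, Sample size estimates, fixes the order of steps: "Randomization will be done prior to the baseline assessment with a statistical software program that generates this sequence". It adds: "Random numbers will be assigned according to the order of patients’ admission to the hospital". Patients are "assigned to the MT (n = 18) or control group (n =18) using a random sampling method". On concealment, "random group allotment will be managed by a social worker who will not be involved in the assessment or intervention".

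The Blinding section covers both assessments: "Pre- and post-test assessments will be performed by a physiotherapist who will be blinded to group allocation (assessor blinding". The Study design section calls the trial open-label with blinded outcome evaluation, so patients are not blinded. The Interventions section has the mirror given to the patient during the initial, pre-test assessment.

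Under Participant timeline, screening, consent and baseline all fall within 48 to 72 h of admission, and "The mirror therapy education will commence immediately after the baseline assessment and end in 4 weeks". Table 3 lists eligibility screen, consent and allocation, in that order, above the assessments, all at week 0. Data analysis plans a two-way repeated ANOVA with time and group effects, with both intention-to-treat and per-protocol analyses. Outcome measures and data collection gives only two assessments, at the beginning and the end of the trial.

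**The concern.** A baseline taken after allocation is a post-randomisation measurement. In an open-label trial the patient may know the arm by then, and both primary outcomes are performance tests on which effort matters. Blinding the assessor does not stop a patient from performing differently. The assessor's blinding is itself in doubt if the mirror appears during the session that this person is scoring.

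Two things are at stake. First, the baseline is half of the change on which the treatment comparison rests, so a distortion there goes straight into the result. Second, a patient who is allocated but withdraws, deteriorates or becomes ineligible before the baseline has no first measurement and cannot contribute an observed change. Nothing in the design needs this order, because MT education starts only after the baseline.

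**Working it through.** **1. Is allocation really made before baseline?** Read alone, the key sentence could mean only that the random list is generated early. Two other places point to actual allocation. Table 3 puts allocation under enrolment, above the assessments (all share the week-0 column, so this is listing order and not a clock). The Interventions section hands out the mirror at the pre-test, which presupposes that the arm is known by then.

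**2. Who can know the arm when baseline is scored?**
- Patient: open-label, and an MT patient receives a mirror at that session.
- Assessor: blinded according to the Blinding section, but present at the session in which the mirror is given. The two statements are compatible only if the handover takes place out of the assessor's sight. The article does not say so.
- Social worker: holds the allocation and takes no part in assessment or intervention. This protects concealment up to assignment, but not the interval between assignment and baseline.

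**3. How a baseline shift enters the result.** With two time points, the group-by-time effect is

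D = (post_MT − base_MT) − (post_C − base_C).

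If knowledge of allocation shifts the mean baseline of the MT arm by δ and nothing else changes, then

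D* = (post_MT − base_MT − δ) − (post_C − base_C) = D − δ.

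A shift of δ in the control arm gives D + δ. The transfer is one for one and the direction can be either. For scale only: the Critical review section quotes a pooled FMA-UE difference of 4.32 points, so δ = 1 would be 1/4.32 = 23% of it. The 1 point is illustrative; no document gives a value for δ.

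**4. Loss before baseline.** A two-time-point repeated ANOVA uses patients with both values. A patient allocated but lost before baseline drops out of it unless a value is supplied, although intention-to-treat would count that patient. If allocation follows baseline, this category is empty.

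**5. Arm sizes (conditional).** The plan's figure is 18 and 18, and no restriction of the list is described. If simple 1:1 randomisation of 36 were used (an assumption):
- P(exactly 18/18) = C(36,18)/2^36 = 0.132
- P(14/22 or worse) = 2 × P(Bin(36, 0.5) ≤ 14) = 0.243

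If instead all of the roughly 300 annual admissions were numbered from a list with 150 per arm and 36 of them enrolled (another assumption), the hypergeometric values are 0.141 and 0.213.

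The cost in power is small. For a t-test at d = 1.15 and one-sided 0.05:

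| Split | Power |
|---|---|
| 18/18 | 0.959 |
| 14/22 | 0.951 |
| 12/24 | 0.938 |

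The 0.959 differs from the 0.80 stated in the article: the stated inputs solve to 10.10, that is 11 per arm and not 18. That is a separate matter and does not affect this point.

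**The case against.** The case against is substantial. The article states two safeguards, a blinded assessor at the pre-test and an independent social worker who manages allotment. If both hold, only a change in the patient's own effort remains, and the article does not say outright that patients learn their arm before being scored. The mirror could be handed over at the end of the session. This stands as a limit on the size of the bias. It does not remove the problem, because the written order permits the knowledge and the mirror sentence makes it likely.

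Several stronger readings are tempting, and the documents do not support them:
- *Patients are excluded according to their allocation.* A reader might infer this from numbering by hospital admission together with a judgement criterion such as "lack of motivation". But Table 3 lists screening and consent before allocation, and no text describes exclusion afterwards. It is a risk only if numbers are attached before enrolment.
- *Most numbers go to people who never enrol, since 36/300 = 12%.* The 300 is a feasibility count under Study setting. An equally natural reading is that the 36 recruited patients are numbered in the order in which they were admitted.
- *The 18/18 split will probably fail.* The 0.132 and 0.243 require simple randomisation, which the article does not state. A restricted list may be in the full protocol, and little power is at stake in any case.
- *Admission order means alternation.* The sequence is generated by software.
- *The bias is about a quarter of the effect.* The 23% follows from an identity applied to an invented 1-point shift. It is not an estimate.

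**Conclusion.** The concern holds in a limited form. The article explicitly places randomisation before baseline, and its mirror handover undercuts the blinding it claims for that same assessment. Any resulting shift in one arm's mean baseline enters the group-by-time effect in full. Its size and direction cannot be derived from the documents, and the stated safeguards reduce it if kept. Loss between allocation and baseline works against the intention-to-treat analysis, again to an unknown extent.

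The conclusion rests on three assumptions: that FMA-UE and WMFT scores respond to patient effort, that the mirror goes only to MT patients, and that it is given while the baseline is under way or before it is scored. If the handover already takes place after scoring and out of the assessor's sight, the assessor part falls away. The patient part then depends on whether patients are told their arm beforehand.

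This should be fixed: it is an avoidable source of bias with an almost free remedy, not a defect shown to invalidate the trial.

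**What to change.** In Sample size estimates, replace the sentence on timing with this order: confirm all eligibility criteria; obtain consent; complete the baseline FMA-UE, WMFT and Modified Barthel Index; only then does the social worker release the next concealed number. State that numbers are issued in order of enrolment, not of hospital admission, from a list restricted to give 18 per arm.

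Reconcile the Interventions section with the Blinding section so that the mirror is handed over only after the blinded baseline assessment is finished. Moving randomisation alone would leave that conflict in place. Show the same order in Table 3.

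The cost is a protocol amendment and some coordination: MT education follows baseline immediately, so the social worker must be reachable at that moment. The patients, the assessments and the 48 to 72 h window stay the same. Trial status reports no patient recruited, so the change can be made before any data are affected. Once recruitment has begun, a baseline influenced by allocation cannot be repaired in the analysis.

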**Fig. 1 Fig1:**
[figure not shown]
Preferred Reporting Items for Systematic Reviews and Meta-Analysis (PRISMA) used to identify studies

### Blinding

Pre- and post-test assessments will be performed by a physiotherapist who will be blinded to group allocation (assessor blinding). Patient education will be provided by a research assistant who will neither be involved in outcome assessment nor with implementing regular rehabilitation interventions. The research assistant will ensure that the patient understands the parameters of the exercise intervention, mirror placement, and unilateral arm execution (nonparalytic arm should be moved and not the paralyzed arm) and masters the MT technique.

